### Data collection and security

The University of Washington (UW) Institute of Translational Health Sciences (ITHS) REDCap instance is being utilized for collection and storage of patient enrollment data, patient-reported outcomes, intervention and enhanced usual care delivery documentation, and the tracking of patients for follow-up assessments. The ITHS REDCap installation is configured to be HIPAA compliant, and is housed in the secure UW data center. The installation currently runs on two virtualized environments, one for the webserver and one for the database itself.

### Data and Safety Monitoring Board

Ongoing monitoring of the study for futility, data integrity, and safety will be conducted by an external independent Data Safety and Monitoring Board (DSMB). The board will consist of a pediatric bioethicist (who will also serve as the Board Chair), a neuropsychologist skilled in the treatment of concussion among youth, and a quantitative biostatistician.

Prior to protocol initiation, the DSMB reviewed the study procedures and plans for safety monitoring. Over the course of the trial, the board will review the recruitment and retention of participants monthly and will monitor the occurrence of adverse events. All potential adverse events will be reported within 48 h to the DSMB. These events include deaths, suicide attempts, severe medication side effects, study dropout, psychiatric hospitalizations, and clinical deterioration defined as the development of new suicidal or homicidal behaviors. The DSMB will also conduct reviews of study progression and data integrity to include assessments of attainment of study recruitment milestones, review of modifications made to the protocol, adequacy of follow-up, and threats to internal validity such as differential drop-out of subjects in the intervention versus control conditions*.* Interim analyses will be conducted in February, 2019 for the purpose of examining effects for future grants, and results will be shared with the DSMB. In this youth concussion-focused comparative effectiveness trial, either negative or positive results will serve to inform a current paucity of randomized trial evidence. Therefore, stoppage rules primarily target futility related to an inability to recruit an adequate sample size and do not extend to the results of interim analyses.

The DSMB will meet formally via teleconference every 6 months. Each year, the oversight board will produce a report that summarizes 1) all serious and unexpected adverse events, 2) the committee’s opinion as to whether safety, confidentiality, and privacy have been adequately assured by the investigators, 3) a summary of progress towards recruitment and follow-up goals. The yearly summary will be forwarded to the principal investigators, who will in turn forward the summary to the Seattle Children’s Research Institute IRB. Further details on the roles and responsibilies of the DSMB can be found within the Data Safety Monitoring Board Charter (Additional file 1).

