#### Informed consent

All study procedures were approved by the Seattle Children’s Hospital institutional review board (IRB; protocol number STUDY00000437) prior to the initation of participant recruitment.The research assistant or study coordinator will give each parent a brief overview of the study and ask the potential parent participant whether or not they would be interested in hearing a more detailed description and learning if their child might be eligible. If the potential parent participant wants to learn more, they will be asked to complete a brief eligibility screening tool. If the adolescent meets eligibility criteria and the parent still wants to learn more about the study, the research assistant or study coordinator will give a copy of the consent form to the parent and review the entire form with them, allowing participants to ask questions or voice concerns. The recruitment procedure will also include discussion of payment for study participation over the course of the year after the injury. Parent participants will also prospectively consent to the release of school records. After parent consent, the eligible adolescent will go through a similar study assent procedure.

There is minimal risk to subjects from data collection procedures, but the small risks that are present include the potential for distress, invasion of privacy, an accidental breach of confidentiality, and the inconvenience of participating. Significant risks to the health of subjects are low, given that the intent of the study is to compare usual care with an enhancement of usual care that is expected to be effective and safe. Upon enrollment, parent and adolescent participants will be given a study information sheet with the study follow-up survey timeline and phone number. All subjects will be in contact by phone with the study research assistants, and intervention subjects will be in frequent contact with their study care manager. Participants will be asked to notify the study personnel if any difficulties arise.

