#### Cognitive-behavioral therapy

The intervention includes modular CBT targeting post-concussive, anxiety, and depressive symptoms. In this CBT treatment, the adolescent is taught coping skills, relaxation strategies, and cognitive strategies to manage their symptoms, while they are encouraged to increase appropriate activation, including pacing of activities. The treatment manual is intentionally flexible to allow for tailoring to the unique presentation and needs of the adolescent, including how many sessions and what specific modules of content to deliver. CBT sessions will be tailored to adolescent preferences and may occur either in-person, by HIPAA compliant video conferencing, or phone call.

The first session involves psychoeducation and goal setting to collaboratively develop an individualized intervention plan and behavioral targets with the adolescent and their parent. Specific CBT intervention elements covered in subsequent modules may include: pain management, problem-solving, behavioral activation, mindfulness, challenging negative thinking, relaxation and imagery, avoidance, emotion regulation, family communication skills, parent and child interaction, sleep hygiene, or brief crisis intervention support. For adolescents who demonstrate adequate CBT readiness/motivation, homework assignments are given [25, 58].

Treatment is delivered primarily in individual sessions with adolescents, although parent involvement in the treatment is strongly encouraged, with the following goals: 1) educating parents about concussion symptom management, 2) creating common goals and a framework for reaching those goals, and 3) understanding the parental role in support and stress processes. The care manager monitors symptoms (depression, anxiety, PCS) on a session-by-session basis using standardized instruments to inform how treatment is working and whether to increase the intensity of CBT or consider a psychiatric consultation regarding medication initiation or changes. Adolescents may discontinue CBT when their symptoms have abated or if they feel that additional sessions are not needed/would not be helpful.

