#### Medication consultation

The stepped-up medication consultation aims to initiate and ensure adequate follow-up of psychopharmacological treatment targeting PCS as well as anxiety and depressive symptoms. In the current stepped care protocol, CBT is the first treatment of choice. For patients that do not adequately respond to the combination of CBT and care management, medications become a stepped-up care option particularly when it appears that there are recalcitrant post-concussive, anxiety, or depressive symptoms that would not readily diminish without initiation of pharmacotherapy. Persistent headaches and/or insomnia can also be important treatment targets for medications when problematic and persistent. Patients who enter the intervention arm of the protocol and are already prescribed psychotropic medications will be prioritized for medication consultation.

The stepped care medication consultation option will start with a brief report from the care manager regarding symptom patterns over time; the adolescent’s current injury status; current and past comorbid medical conditions; current primary care, sports medicine and rehabilitation service use; current medication use including analgesics and psychotropic medications; prior psychotropic medication use; and attitudes and beliefs surrounding medication treatment [25, 31, 46].

For adolescent patients who have never received prior treatment for depression or anxiety, a SSRI or newer non-SSRI antidepressant is the treatment of choice [59–65]. Recommendations for medications will be made to the adolescent’s primary care physician and specialty care provider who is managing the concussion. In our prior Care for Post-Concussive Symptoms pilot study, adolescent care providers including pediatricians and treating physicians in rehabilitation medicine were often the primary prescribing providers [36, 46]. If negative side effects are reported by the adolescent, the care manager will tell the family to contact their prescribing physician as soon as possible. The care manager will also bring these concerns to the attention of the study’s child psychiatrist for consultation within 3 days, to seek recommendations for medication change or discontinuation, which will then be conveyed to the prescribing provider. The study team has expertise in the provision of long-distance pharmacological consultation, thus enhancing the reach of the current intervention in comparison to the smaller scale pilot study.

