### Usual care for control subjects

Control subjects will receive usual care. Usual post-injury care may include the routine use of sports medicine, rehabilitation medicine, physical therapy, primary care emergency department, and specialty mental health services. Usual care has been selected for controls as it remains the optimal comparator condition for policy guidelines and represents care now being delivered in specialty clinics across the USA. Usual care does include referral to specialty providers caring for adolescents with concussion as needed. All aspects of concomitant care are permitted during the trial following enrollment across study arms. For control group participants who indicate suicidal ideation on follow-up surveys, a clinical assessment is conducted by a study principal investigator by telephone, with appropriate follow-up, discussion with a parent/guardian, and provision of referral resources if needed based on risk assessment.

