#### Health service and medication utilization

The Zatzick et al. [25] and MacKenzie et al. [79] Parent report will be used to assess adolescents’ pre- and post-sports injury health service utilization. Parents will report on emergency department and outpatient pediatric and any specialty sports medicine care. Parents will also report on types of medication used by adolescents. This will be supplemented by information from the medical record.

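### Suicidal behavior and medication side effects are more likely to be detected in the intervention arm than in controls, so by-arm counts of these events would not be comparable

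*Protocol article*

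**What the plan says.** The section on the Data and Safety Monitoring Board (DSMB) lists the reportable events: "These events include deaths, suicide attempts, severe medication side effects, study dropout, psychiatric hospitalizations, and clinical deterioration". It defines clinical deterioration as new suicidal or homicidal behavior. It also sets a clock: "All potential adverse events will be reported within 48 h to the DSMB". It does not state a way of finding these events that is the same in both arms.

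Other sections describe how events may come to notice.

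- **Intervention arm.** Informed consent: "intervention subjects will be in frequent contact with their study care manager". Cognitive-behavioral therapy: "The care manager monitors symptoms (depression, anxiety, PCS) on a session-by-session basis using standardized instruments". Medication consultation, on side effects that the adolescent reports: "The care manager will also bring these concerns to the attention of the study’s child psychiatrist for consultation within 3 days".
- **Control arm.** Usual care for control subjects: "For control group participants who indicate suicidal ideation on follow-up surveys, a clinical assessment is conducted", by telephone and by a principal investigator. No side-effect route is described for controls, although all concomitant care is permitted in both arms.
- **Both arms.** Participants are asked to tell staff of difficulties, and all have phone contact with research assistants (Informed consent). Surveys follow at 3, 6 and 12 months (Outcome evaluation). On service use, "Parents will report on emergency department and outpatient pediatric and any specialty sports medicine care"; parents also report types of medication, and the medical record supplements their report (Health service and medication utilization).

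**The concern.** The DSMB section makes suicidal behavior, severe medication side effects and psychiatric admissions reportable. The intervention includes stepped-up psychotropic medication consultation, so suicidality and side effects are among the harms of most interest. They are also the events whose detection depends most on how often someone is in contact with the adolescent.

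If the true risk is the same in both arms but one arm is watched more closely, that arm records more events and records them sooner. A by-arm table given to the DSMB or published with the results could then show an apparent harm, or hide a real benefit. Control adolescents with a serious event between surveys could also go unrecorded, or be recorded late.

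**Working it through.** **1. Routes set side by side**

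| Event | Routes in the intervention arm only | Routes in both arms, or in controls | Likely unequal? |
|---|---|---|---|
| Suicide attempt, new suicidal behavior | Care-manager contact; depression and anxiety scales at each session | Surveys at 3, 6 and 12 months, with a stated control assessment if ideation is indicated; spontaneous report; phone contact; records | Yes |
| Severe medication side effect | Care manager hears of it and takes it to the study psychiatrist within 3 days | Spontaneous report; phone contact; records; the survey section covers types of medication, with no side-effect content described | Yes |
| Psychiatric hospitalization | Care-manager contact | Spontaneous report; phone contact; records; parent service-use report, which as described names emergency, outpatient pediatric and sports medicine care | Possibly; records may recover it |
| Death, study dropout | Nothing described that depends on sessions | Same follow-up tracking in both arms | Largely no |

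The last two surveys are 12 − 6 = 6 months apart. Over that interval a control event comes to light only through spontaneous report, phone contact or the record, unless the 12-month survey picks it up later. The extra intervention-arm route also runs through unblinded care managers, while the research assistants who conduct follow-up interviews are blinded (Masking of treatment allocation).

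**2. Direction and possible size**

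The article states no adverse-event rate and no detection probability, so there is no plan figure to reproduce. What follows is an illustration.

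Inputs: 100 per arm (Power analysis and sample size). Assumed: the same true risk in both arms, and detection probabilities sI (intervention) and sC (control).

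Recorded risk = true risk × detection probability. With equal true risk:

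recorded risk ratio = (true risk × sI) / (true risk × sC) = sI / sC

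| sI | sC | sI / sC | Recorded events per 100 at 5% true risk |
|---|---|---|---|
| 1.00 | 1.00 | 1.00 | 5.0 v 5.0 |
| 1.00 | 0.90 | 1.11 | 5.0 v 4.5 |
| 0.95 | 0.80 | 1.19 | 4.75 v 4.0 |
| 0.95 | 0.60 | 1.58 | 4.75 v 3.0 |
| 0.95 | 0.40 | 2.38 | 4.75 v 2.0 |

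The true risk cancels from the ratio, so the direction depends only on sI exceeding sC.

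**3. Chance of a spurious finding**

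At 5% true risk and 0.95 v 0.60, the standard error of the difference is √(0.0475 × 0.9525/100 + 0.03 × 0.97/100) = 0.0273. The expected difference is 0.0175, so z = 0.64. The chance of passing 1.96 in the direction of harm is about 9%, against 2.5% in that direction with equal detection. At 10% true risk the same detection rates give 9.5 v 6.0 events and about 15%. The normal approximation is rough at such low counts.

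**The case against.** The strongest reply is that nobody has planned this comparison. None of the four aims concerns safety, the data analysis sections contain no harms analysis, and the only between-arm item in the DSMB section is differential dropout. Reporting within 48 hours protects participants; it does not estimate an effect. That stands, and it makes the point conditional on event counts being compared or shown by arm.

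A reader might infer that controls are observed only through spontaneous report and three surveys. The documents do not support that: they also give phone contact with research assistants, a clinical assessment when ideation is indicated, and the medical record. Nor do they show safety events being sought at every session. The session instruments measure symptoms, the side-effect route starts only when the adolescent reports one, and the number of sessions is flexible. Better event detection in the intervention arm is a reasonable inference, not a stated procedure.

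It can also be said that adverse-event forms belong in the full protocol or the DSMB Charter, neither of which is shown. The absence of an adverse-event item from the table of measures is therefore not held against the plan. The point rests on the unequal routes that the article does describe. The Charter could set a common procedure, but the article does not say that it does.

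Finally, more contact is inherent in testing care management against usual care. That is true of the contact, but it does not oblige the trial to base by-arm safety counts on it.

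**Conclusion.** The point holds in a limited form. As described, suicidal behavior and medication side effects, and possibly psychiatric hospitalizations, are more likely to be detected in the intervention arm, and detected sooner. By-arm counts of these events would tend to disfavor the intervention and under-count control events.

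It would go too far to say that every between-arm comparison of harms is biased, since deaths and dropout are largely unaffected. It would also go too far to put the distortion at 1.6 to 2.4. Those values need control detection of 60% down to 40%; milder assumptions give 1.1 to 1.2. The size cannot be computed from the documents. The direction rests on one assumption, that detection is better in the intervention arm, and the consequence arises only if counts are compared or reported by arm.

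**What to change.** - Add identically worded questions on suicide attempt, psychiatric hospitalization and severe medication side effects to the 3-, 6- and 12-month surveys in both arms.
- Base any by-arm safety summary on those answers plus medical record review applied equally to both arms.
- Keep reporting all events to the DSMB within 48 hours, each flagged by how it was found. Show events detected only by a care manager separately from the by-arm summary.

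The cost is a few survey questions and a source field on the event record, with no extra staff and no change to treatment. The downsides are slightly longer surveys and more control-arm events to process. The Trial status section has recruitment starting in March 2017 and follow-up ending by March 2020, so questions added partway would cover only the surveys still to come, and the summary should say so.

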#### Dissemination policy

The study team plans to write up study results for publication in a scientific journal article to reach healthcare professionals. Study results will also be posted on ClincialTrials.gov. If the collaborative care intervention is found to be superior to care as usual, we plan to write a grant to further develop dissemination mechanisms to train other healthcare professionals in this model. We will abide by the International Committee of Medical Journal Editors guidelines regarding authorship, and plan to provide study team members first access to the data for addressing the main objectives stated here. We do not plan to use professional writers. The final de-identified study dataset will be shared on the National Institute of Child Health and Human Development Data and Specimen Hub for the purposes of secondary research use.

## Discussion

The CARE4PCS-II study is the largest collaborative care trial to date to target symptomatic improvements in sports injured adolescents after concussion. The investigation builds upon and extends the established randomized clinical trial evidence base supporting collaborative care interventions for youth and adults presenting with medical and psychiatric co-morbidity to primary and acute care settings [20–30]. The investigation was preceeded by a smaller scale study team pilot investigation that used CBT as the primary evidence-based treatment modality in a stepped care protocol with the option to recommend psychotropic medication to injured youth with enduring post-concussive symptoms. The pilot study suggested that the stepped collaborative care intervention may be effective in reducing PCS and other co-morbid symptoms in concussion-exposed youth [36]. The study team is aware that the prioritization of CBT over medications in our stepped care protocols for concussed youth differs from previous primary and acute care adult collaborative care procedures that have given equal priority to CBT and pharmacotherapy [14, 15, 25]. The decision to make CBT the primary evidence-based treatment modality was based on a review of the adolescent CBT and pharmacotherapy literatures. Subgroup analyses examining heterogeneity of treatment effects may be required should the current trial recruit a substantial number of concussed adolescents who are on psychotropic medication at the time of their sports injury. The study is unique in its adaptation of the collaborative care model to a broad spectrum of settings in which adolescents receive treatment for the sequalae of their sports injuries. Care in the current protocol can link patients seen in multiple pediatric, primary care, sports medicine, and school settings. Prior adolescent collaborative care intervention studies have focused more narrowly on recruitment and linkage from selective primary and acute care medical settings [27–31].

The study is designed to broadly reach patients referred throughout the Seattle, Western Washington, and Puget Sound region. Multiple intervention elements support the broadening of the reach of the collaborative care treatment, including the use of HIPAA-compliant videoconferencing technology that allows for the expansion of CBT delivery beyond regional clinic settings that has previously characterized collaborative care clinical trials for youth. Similarly, pediatric psychopharmacologic intervention procedures have been adapted from statewide pediatric consultation models [46], which are unlikely to reach sports injured youth with persistent concussive symptoms without the orchestrated linkage procedures provided by collaborative care. Should the trial demonstrate effectiveness the study team is uniquely positioned to develop and roll-out nationwide dissemination efforts. The study team has an established track record of working with professional societies and federal agencies to disseminate the results of primary and secondary intervention for youth and adults [97–100].

